**Figure 2 F2:**
[figure not shown]
Recruitment coverage for study participants.

The inclusion criteria encompass: (1) aged above 18 years; (2) resides in a high-altitude region of Western Sichuan (with an altitude above 1,500 meters); (3) clinically diagnosed with AIS and confirmed by computed tomography angiography (CTA) or digital substraction angiography (DSA) to have large vessel occlusion; (4) The interval between last known well and enrollment will be within 24 h, and (5) signed informed consent and able to comply with follow-up requirements. The main exclusion criteria mainly include: (1) Pre-onset mRS score > 2; (2) computed tomography (CT) or magnetic resonance imaging (MRI) confirms the presence of intracranial hemorrhage or the infarct size exceeds one-third of the supply area of the middle cerebral artery; (3) History, previous imaging, or clinical judgment suggests the presence of a brain tumor, arteriovenous malformation, or intracranial artery dissection, or (4) History of head trauma within the past 3 months. Detailed exclusion and withdrawal criteria are provided in Appendix.

### 2.3 Outcomes

The primary outcome is the proportion of patients achieving functional independence (mRS 0–2) at 90 days post-stroke. The secondary outcomes are divided into clinical efficacy outcomes and imaging markers. The clinical efficacy outcomes include: (1) mRS score at 90 days; (2) early neurological improvement rate (defined as NIHSS score of 0–2 or a reduction of ≥8 points from baseline within 24 h of enrollment); (3) changes in NIHSS scores between day 7 ± 1 or discharge and baseline; (4) Quality of life assessed by five-level EuroQol five-dimensional questionnaire (EQ-5D-5L) at 90 days, and (5) Montreal cognitive assessment (MOCA) and mini-mental state examination (MMSE) scores at 180 days. The imaging endpoints include: (1) reperfusion rate [modified thrombolysis in cerebral infarction (mTICI) ≥ 2b on DSA] and (2) infarct volume based on diffusion-weighted MRI within 5–7 days. All data will be collected through electronic media and uploaded in real-time to a centralized data management platform for storage.

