### 2.2 Sample size estimation and participants

We estimated that group sample sizes of 526 in each group will achieve 90.031% power to detect a difference between the group proportions of functional independence [modified Rankin scale (mRS) range from 0 to 2] at 90 days of 0.135. According to the Multicenter Randomized CLinical trial of Endovascular treatment for Acute ischemic stroke in the Netherlands (MR CLEAN) (14) trial, the proportion in control group is assumed to be 0.191 under the null hypothesis and 0.326 under the alternative hypothesis. The significance level of the test is 0.05. Considering a 20% dropout rate, the final sample sizes for both groups were 526. Given the large data requirements of machine learning, we doubled the sample size of each group based on the original estimates.

A total of 1,052 patients with acute large vessel occlusion stroke were enrolled from Ya'an People's Hospital, Ganzi Tibetan Autonomous Prefecture People's Hospital, and Liangshan Yi Autonomous Prefecture First People's Hospital (Figure 2), including both those who underwent endovascular treatment and those who did not. Although all patients met the current guideline-based indications for mechanical thrombectomy, some did not receive the procedure due to various factors, such as declining treatment over concerns about surgical risk or experiencing delays in transfer to thrombectomy-capable centers. In this study, these branch centers primarily served as referral sites or admitted patients who declined endovascular therapy. All participating centers implemented a standardized, homogeneous protocol for medical management. Prior to group assignment, patients who met the criteria for intravenous thrombolysis and had no contraindications were eligible to receive intravenous thrombolysis.

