### 2.4 Statistical analysis

Statistical analyses will be conducted using R version 4.3.3 by an independent statistician blinded to group assignments. Continuous variables will be tested for normality using the Shapiro–Wilk test (α = 0.05). Normally distributed data will be presented as means ± standard deviations and compared using the independent *t*-test or one-way analysis of variance. Non-normally distributed data will be presented as medians with interquartile ranges and compared using the Wilcoxon rank-sum test or Kruskal–Wallis test. Categorical variables will be summarized as counts and percentages, with group comparisons performed using the χ^2^ test or Fisher's exact test.

Given the non-randomized allocation of treatment (EVT vs. SMT), potential confounding by indication will be addressed using propensity score methods. A logistic regression model including baseline covariates (age, sex, baseline NIHSS, onset-to-enrollment time, comorbidities, and relevant imaging findings) will be used to estimate the propensity score for receiving EVT. We will perform both propensity score matching (1:1 nearest-neighbor without replacement, caliper = 0.2 SD of the logit) and inverse probability of treatment weighting (IPTW) to adjust for baseline imbalances. Standardized mean differences (SMDs) will be reported to assess covariate balance before and after adjustment.

Primary analyses will be performed on the matched cohort, with IPTW analyses conducted as sensitivity analyses. Logistic regression will be used for binary outcomes, linear regression for continuous outcomes, and ordinal logistic regression for ordinal outcomes, all adjusted for residual imbalances after matching. Results will be reported as adjusted odds ratios (aOR) with 95% confidence intervals (CIs).

To address missing data, multiple imputation using chained equations (MICE) will be employed under the missing-at-random assumption, generating 20 imputed datasets. Analyses will be conducted on each dataset, and results will be pooled using Rubin's rules. Sensitivity analyses will compare complete-case and imputed results to assess robustness.

All hypothesis tests will be two-sided, with *p* ≤ 0.05 considered statistically significant. No interim analyses are planned.

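### The 180-day MoCA and MMSE comparison between non-randomised groups adjusts for neither education nor first language, so a difference may be partly confounded, by an unknown amount and in an unknown direction

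*Protocol article*

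**What the plan says.** Section 2.3 of the Protocol article (Outcomes) places "Montreal cognitive assessment (MOCA) and mini-mental state examination (MMSE) scores at 180 days" last among five secondary clinical efficacy outcomes.

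Section 2.4 (Statistical analysis) recognises that treatment is not randomised: "Given the non-randomized allocation of treatment (EVT vs. SMT), potential confounding by indication will be addressed using propensity score methods". The propensity model's inputs are given as "age, sex, baseline NIHSS, onset-to-enrollment time, comorbidities, and relevant imaging findings". The main analysis uses the 1:1 matched cohort, and IPTW is a sensitivity analysis. The outcome models include "linear regression for continuous outcomes" and are "all adjusted for residual imbalances after matching". Education, literacy, first language, ethnicity and centre do not appear.

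Section 2.2 explains why eligible patients may go without EVT. The examples given are "declining treatment over concerns about surgical risk" and late transfer. It adds that the branch centres mainly referred patients on or took in those who had refused the procedure. Of the three hospitals named, one is in "Ganzi Tibetan Autonomous Prefecture" and another in the Liangshan Yi prefecture; the third is in Ya'an.

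**The concern.** It is general measurement knowledge, not something the documents state, that scores on brief cognitive tests vary with schooling and with whether the patient is tested in a first language. If either factor also differs between those who receive EVT and those who do not, it is a common cause of treatment and score. Section 2.2 makes this plausible, because it ties non-treatment to the choice of patient or family and to place of care.

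Matching and IPTW rest on the same named covariates, so agreement between them would not reveal the problem. Nor would good standardised mean differences, which describe only the variables that were measured. Neither comorbidities nor imaging findings can reasonably be read to cover education or language.

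At stake is whether a difference in the 180-day scores can be credited to EVT or partly reflects who received it. If the two facts are never collected, no later analysis can separate these explanations.

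**Working it through.** **1. The plan's own figure.** The documents give no size calculation for MoCA or MMSE, so the only figure to reproduce is the primary one, 526 per group. With p1 = 0.191, p2 = 0.326, mean 0.2585, two-sided alpha 0.05 and power 0.90:

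n = [1.96 × √(2 × 0.2585 × 0.7415) + 1.2816 × √(0.191 × 0.809 + 0.326 × 0.674)]² / 0.135² = 219 per group.

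219 × 1.2 = 263 (rounded up), and 263 × 2 = 526. The stated size is reproduced. Allowing for the 20% dropout, 526 × 0.8 = 421 per group could have a 180-day score. This is a ceiling, because caliper matching and patients who cannot be tested would lower it.

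**2. Size of the possible bias.**

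| Input | Value | Source |
|---|---|---|
| Score deficit from low schooling or testing in a second language | 3 points (range 1 to 5) | assumption |
| Difference between groups in the share affected | 20 percentage points (range 10 to 30) | assumption |
| SD of the score | 6 points | assumption |
| Patients per group | 421 at most | 526 × 0.8 |

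Bias = deficit × difference in share:
- low: 1 × 0.10 = 0.1 points
- central: 3 × 0.20 = 0.6 points
- high: 5 × 0.30 = 1.5 points

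SE = 6 × √(2/421) = 0.41. Bias divided by SE is 0.1/0.41 = 0.2, 0.6/0.41 = 1.5 and 1.5/0.41 = 3.6.

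With no true effect, the chance of p < 0.05 is Φ(−1.96 + bias/SE) + Φ(−1.96 − bias/SE). At 420 per group this is 5.7%, 30.5% and 95.2% for the three cases. At 200 pairs it is 5.3%, 17% and 70.5%. Losing pairs leaves the bias in points unchanged but lowers its ratio to the SE.

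**3. Does the stated procedure remove it?** The matching in section 2.4 was simulated with 1,052 patients, a caliper of 0.2 SD of the logit, 200 runs per scenario and a true EVT effect of zero. Assumptions: residual SD 6, and half the patients carrying the education or language factor, with their odds of receiving EVT lower by the ratio shown.

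| Odds ratio | Deficit (points) | Listed covariates only: bias, rejection at 5% | Factor added: bias, rejection at 5% |
|---|---|---|---|
| 1 | 2 | −0.03, 4.5% | −0.01, 2% |
| 1 | 4 | 0.02, 3% | 0.01, 2.5% |
| 1.5 | 2 | 0.22, 9.5% | 0.02, 7% |
| 1.5 | 4 | 0.36, 12% | −0.02, 4.5% |
| 2 | 2 | 0.41, 18% | 0.06, 6% |
| 2 | 4 | 0.66, 29.5% | 0.00, 3% |
| 3 | 2 | 0.53, 24% | −0.02, 2.5% |
| 3 | 4 | 1.02, 65% | −0.04, 5% |

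Matching on the listed covariates leaves the bias in place whenever the factor affects both treatment and score. If the factor is unrelated to treatment (odds ratio 1), there is no bias and including it does no harm. The positive sign follows from the assumed direction; reversing that assumption would reverse the sign.

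In these runs the factor entered both the propensity model and the outcome regression. The fix below uses the regression alone. Under the additive linear model simulated, that also suffices, because the EVT coefficient is then estimated conditional on the factor.

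**The case against.** The strongest case against is that this is a condensed article. The covariate list ends in broad categories and may not be exhaustive, and Figure 1 and the Appendix, which are not shown, might record education or language. Test version, scoring rules and CRF fields normally sit in the full protocol, and their absence here is no finding. That stands. What remains is narrower: the article names its adjustment variables, and these two are not among them.

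It is also fair that every magnitude input is assumed, that the central case of 1.5 SE falls short of nominal significance, and that onset-to-enrollment time may partly capture remoteness. It does not capture schooling, language or refusal.

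A reader might infer more than the documents support:
- **That the bias favours EVT.** No education or language data by group are given, so the direction is unknown.
- **That refusers make up much of the SMT group.** Section 2.2 gives examples of reasons and no proportions.
- **That the whole cohort is from Tibetan and Yi prefectures.** Ya'an is the first hospital named, and eligibility depends on residence above 1,500 m in Western Sichuan.
- **That the lack of a baseline cognitive score is a defect.** Patients enrol within 24 hours of being last known well with a large vessel occlusion, when a pre-stroke score cannot be measured.
- **That the primary result is compromised.** Nothing here shows that education or language confounds the 90-day mRS.

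**Conclusion.** The point holds as a limited one. As stated, the analysis of the 180-day MoCA and MMSE scores leaves out two factors that generally affect those scores and could plausibly relate to who receives EVT. No balance check on the listed covariates can show whether this matters. A difference in cognitive scores may therefore be partly confounded.

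On the stated assumptions the bias ranges from negligible (0.1 points, 0.2 SE) to large enough to create a nominally significant result by itself (1.5 points, 3.6 SE). These ratios use the ceiling of about 421 per group and an SD of 6. The range describes what is possible and does not estimate what will occur. The point is worth acting on because the remedy is cheap and depends on collecting the data.

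**What to change.** Record years of education and first language at baseline, from the patient or a proxy, and collect both retrospectively for those already enrolled. State in section 2.4 that both are prespecified covariates in the MoCA and MMSE regressions, in the matched analysis and in the IPTW sensitivity analysis, whatever the balance after matching.

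Leave the propensity model for the primary mRS outcome unchanged. Adding the two variables there would alter the matched cohort for that outcome without an argument that they confound it.

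Report the language of testing at day 180 by group, but do not adjust for it. It is determined after treatment and could be influenced by the outcome of the stroke.

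The cost is two extra CRF fields and one sentence in the analysis section. Some values will be missing, mainly where a patient enrolled earlier has died or cannot answer and no proxy can be reached. The planned multiple imputation can handle these under its missing-at-random assumption.

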### 2.4 Statistical analysis

Statistical analyses will be conducted using R version 4.3.3 by an independent statistician blinded to group assignments. Continuous variables will be tested for normality using the Shapiro–Wilk test (α = 0.05). Normally distributed data will be presented as means ± standard deviations and compared using the independent *t*-test or one-way analysis of variance. Non-normally distributed data will be presented as medians with interquartile ranges and compared using the Wilcoxon rank-sum test or Kruskal–Wallis test. Categorical variables will be summarized as counts and percentages, with group comparisons performed using the χ^2^ test or Fisher's exact test.

Given the non-randomized allocation of treatment (EVT vs. SMT), potential confounding by indication will be addressed using propensity score methods. A logistic regression model including baseline covariates (age, sex, baseline NIHSS, onset-to-enrollment time, comorbidities, and relevant imaging findings) will be used to estimate the propensity score for receiving EVT. We will perform both propensity score matching (1:1 nearest-neighbor without replacement, caliper = 0.2 SD of the logit) and inverse probability of treatment weighting (IPTW) to adjust for baseline imbalances. Standardized mean differences (SMDs) will be reported to assess covariate balance before and after adjustment.

Primary analyses will be performed on the matched cohort, with IPTW analyses conducted as sensitivity analyses. Logistic regression will be used for binary outcomes, linear regression for continuous outcomes, and ordinal logistic regression for ordinal outcomes, all adjusted for residual imbalances after matching. Results will be reported as adjusted odds ratios (aOR) with 95% confidence intervals (CIs).

To address missing data, multiple imputation using chained equations (MICE) will be employed under the missing-at-random assumption, generating 20 imputed datasets. Analyses will be conducted on each dataset, and results will be pooled using Rubin's rules. Sensitivity analyses will compare complete-case and imputed results to assess robustness.

All hypothesis tests will be two-sided, with *p* ≤ 0.05 considered statistically significant. No interim analyses are planned.

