## 1 Introduction

Stroke is a leading cause of death and disability globally, with large vessel occlusive acute ischemic stroke (LVO-AIS) posing a serious threat to health burden due to its high rates of disability and mortality. LVO-AIS (1) is a critical medical emergency characterized by acute occlusion of major cerebral arteries, such as the internal carotid artery or middle cerebral artery, leading to local cerebral ischemia and hypoxia which result in extensive cerebral infarction and severe disability or death if blood flow is not restored promptly. With the advancement of medical technologies, endovascular treatment (EVT) has become a crucial therapeutic approach for LVO-AIS, marking a new era in the treatment of ischemic penumbra by combining imaging techniques to identify low perfusion areas. It significantly improves reperfusion rates and enhances patients' neurological outcomes particularly when administered within 6 h of onset (2). The time window for thrombectomy in anterior circulation large vessel occlusion has now been extended to 24 h (3, 4). The Basilar Artery Occlusion Chinese Endovascular Trial (BAOCHE) (5) and Trial of Endovascular Treatment of Acute Basilar-Artery Occlusion (ATTENTION) (6) has confirmed the superiority of thrombectomy in the posterior circulation within 24 h.

An increasing number of individuals are engaging in tourism and recreational activities in high-altitude regions. Additionally, certain groups—including military personnel, miners, tour guides, and local residents—are chronically exposed to such environments. A global survey in 2021 estimated that approximately 500 million people reside at altitudes of ≥1,500 m (7), with China possessing the world's largest plateau region, home to roughly 12 million permanent residents (8). Notably, our previous literature review demonstrated that patients with ischemic stroke in high-altitude areas have significantly poorer functional outcomes compared with those in low-altitude regions. Moreover, differences in infarct localization have been observed, with anterior circulation strokes being more prevalent, and, according to TOAST classification, a higher incidence of large-artery atherosclerosis (9). These findings underscore the need for high-quality research to better inform clinical decision-making for ischemic stroke in high-altitude populations.

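### The propensity score leaves out intravenous thrombolysis and pre-onset mRS, two pre-treatment variables that matching and IPTW then do not balance directly

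*Protocol article*

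**What the plan says.** Section 2.4 (Statistical analysis) answers confounding by indication with a propensity score. The logistic model "including baseline covariates (age, sex, baseline NIHSS, onset-to-enrollment time, comorbidities, and relevant imaging findings) will be used to estimate the propensity score". The primary analysis is 1:1 matching on that score, and IPTW is a sensitivity analysis. Outcome models adjust for imbalance that remains after matching, without naming the variables. Standardized mean differences are to be reported before and after adjustment.

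Section 2.2 describes how patients reach each group:

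- On thrombolysis: "Prior to group assignment, patients who met the criteria for intravenous thrombolysis and had no contraindications were eligible to receive intravenous thrombolysis".
- On prior disability, the exclusion is only "Pre-onset mRS score > 2", so scores of 0, 1 and 2 are all enrolled.
- On hospitals: "these branch centers primarily served as referral sites or admitted patients who declined endovascular therapy". Reasons given for not receiving EVT include refusal and "experiencing delays in transfer to thrombectomy-capable centers".
- On medical care: "All participating centers implemented a standardized, homogeneous protocol for medical management".
- On altitude, the criterion sets a lower bound only, "with an altitude above 1,500 meters".

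**The concern.** Treatment is not randomized, so the efficacy claim depends on the score containing the pre-treatment variables that may differ between groups and bear on outcome. Thrombolysis is a reperfusion treatment given before the groups are formed, so it is a legitimate adjustment variable and not a consequence of EVT. Pre-onset mRS is measured on the same scale as the primary outcome (mRS 0 to 2 at 90 days). Both must be known at screening or before grouping, so leaving them out saves no data collection.

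If either differs between the matched groups, the primary odds ratio mixes its effect with that of EVT. IPTW would not serve as an independent check, because it uses the same score.

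**Working it through.** **Step 1. Compare the list with the variables available before treatment.**

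| Variable | Known before grouping? | Varies among enrolled? | In the Section 2.4 list? |
|---|---|---|---|
| Intravenous thrombolysis | Yes (2.2) | Yes, eligible patients only | No |
| Pre-onset mRS | Yes (2.2, exclusion criterion) | Yes, 0 to 2 | No |
| Occlusion site | Yes, CTA or DSA at entry (2.2) | Yes, if posterior as well as anterior occlusions are enrolled | Plausibly, under imaging findings |
| Altitude of residence | Yes (2.2) | Yes, above 1,500 m | No |
| Hospital | Yes | Three hospitals | No |

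The list carries no wording such as 'for example', and no other part of the article adds thrombolysis or pre-onset mRS to the matching, the weights or the outcome model. Neither is a comorbidity or an imaging finding in ordinary use.

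**Step 2. The plan's own reference effect.** Section 2.2 assumes 0.191 and 0.326, and 0.326 − 0.191 = 0.135. The sample size also reproduces: a two-sided 5% test with 90% power and pooled variance needs 219 per group; 219 × 1.2 = 263; 263 × 2 = 526. The point does not rest on this figure. It only supplies the scale.

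**Step 3. Size of the bias from an omitted binary factor.**

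Bias in the risk difference = (difference in prevalence between matched groups) × (effect of the factor on independence).

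The inputs for thrombolysis are assumptions and are not in the documents:

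- Low: (0.40 − 0.20) × 0.10 = 0.020, and 0.020 / 0.135 = 15% of the planned effect.
- High: (0.50 − 0.20) × 0.15 = 0.045, and 0.045 / 0.135 = 33%.

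The result is reported as an odds ratio, so on that scale, with no true EVT effect, a 0.191 control rate and bias in favour of EVT:

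- Low: (0.211/0.789) / (0.191/0.809) = 1.13.
- High: (0.236/0.764) / (0.191/0.809) = 1.31.
- Planned effect, for comparison: (0.326/0.674) / (0.191/0.809) = 2.05.

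If matching on the listed covariates halved the imbalance, the bias would halve to 1.0 to 2.25 points. For pre-onset mRS the same formula applies. With an assumed imbalance of 10 points and an effect of 5 to 15 points, it gives 0.5 to 1.5 points.

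**Step 4. Effect on the test.** Take n = 421 per group (526 × 0.8, supposing every patient is matched) and bias b in favour of EVT with no true effect. The chance of a significant result for EVT is Φ{[b√n − 1.96√(2p̄q̄)] / √(p₁q₁ + p₂q₂)}, with p₁ = 0.191, p₂ = p₁ + b, p̄ the mean of the two rates, and each q equal to 1 minus its p.

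- b = 0.020: 11%.
- b = 0.045: 36%.
- At 210 per group: 7% and 20%.

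The nominal figure in that direction is 2.5%. A larger sample does not remove the bias. It makes a false positive more likely. If the bias runs the other way, a true benefit is understated instead.

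**The case against.** Five arguments stand on the other side.

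1. Two of the six list entries are open categories, so the list may be an article-level summary with detail left to an analysis plan. That holds for occlusion site, which fits under imaging findings. It does not hold for thrombolysis or pre-onset mRS, which fit under no listed entry.
2. The outcome models adjust for residual imbalance, and the balance table is not stated to stop at the listed covariates. Either could pick up the two variables, so a reader should not infer that the imbalance would necessarily go unseen. But the article does not say that they are checked.
3. Matching on time from onset, NIHSS and comorbidities probably reduces any imbalance in thrombolysis, so the figures above are not forecasts. This is accepted.
4. A reader might infer that treatment is tied to hospital by design, so that the comparison is one hospital's care against another's. The text does not go that far. The study is observational, the branch centers' role is described with the word 'primarily', referred patients may themselves receive EVT, and a common medical protocol is stated. If hospital nearly determined treatment, putting it in the score would destroy overlap, so its absence is not plainly an error. Transfer status may be part of the route to EVT and so is not a clear confounder.
5. A reader might also count altitude as an omitted known confounder. The Introduction says only that "patients with ischemic stroke in high-altitude areas have significantly poorer functional outcomes compared with those in low-altitude regions". Everyone enrolled lives above 1,500 m, and nothing shows a gradient within that range or a link to treatment choice.

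The prognostic roles of thrombolysis and pre-onset mRS are general clinical reasoning and are not stated in the article. The restriction to scores of 0 to 2 narrows the second concern without removing it.

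**Conclusion.** The point holds for two variables. As written, the score omits thrombolysis and pre-onset mRS, and both propensity analyses share the omission. The direction of the resulting confounding is unknown. Its illustrative size for thrombolysis, 2.0 to 4.5 points, rests on assumed prevalences and effects and on the imbalance surviving matching in full, so it is nearer an upper range than an expected value. It is below the planned effect but large enough to distort the odds ratio and the test.

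Hospital is linked to treatment and deserves an overlap check. The documents do not support the stronger reading that hospital stands in for treatment, or that omitting hospital, transfer status or altitude from the score is an error in itself.

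**What to change.** - Add thrombolysis (yes/no) and pre-onset mRS (0/1/2) to the propensity model and to the table of standardized mean differences.
- State that occlusion site is among the imaging findings.
- Optionally, add altitude of residence as a covariate.
- Do not force hospital or transfer status into the score. Tabulate treatment by hospital, and add one sensitivity analysis restricted to hospitals that gave both treatments. State that a hospital without overlap cannot separate the EVT effect from the hospital effect.

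The cost is a few lines of wording, one table, one sensitivity analysis and possibly a few lost matched pairs. Exact matching is not required.

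### Outcome models that adjust only for whatever stays imbalanced after matching let the data choose the primary odds ratio, and the IPTW odds ratio set against it is a different quantity

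*Protocol article*

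**What the plan says.** Section 2.4 of the protocol article estimates a propensity score from "baseline covariates (age, sex, baseline NIHSS, onset-to-enrollment time, comorbidities, and relevant imaging findings". It then plans two uses of the score: matching ("1:1 nearest-neighbor without replacement, caliper = 0.2 SD of the logit") and "inverse probability of treatment weighting (IPTW) to adjust for baseline imbalances".

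Their roles are fixed: "Primary analyses will be performed on the matched cohort, with IPTW analyses conducted as sensitivity analyses". Logistic, linear and ordinal outcome models are "all adjusted for residual imbalances after matching". On reporting: "Results will be reported as adjusted odds ratios (aOR) with 95% confidence intervals (CIs)". Missing data are handled with 20 imputed datasets, each analysed and then pooled by Rubin's rules.

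Section 2.2 sizes the study on a difference in proportions: "the proportion in control group is assumed to be 0.191 under the null hypothesis and 0.326 under the alternative hypothesis".

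The section names no target population for either method, no type of IPTW weight and no variance method.

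**The concern.** Two things follow from the stated text.

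**The primary model is chosen from the data.** Which covariates are adjusted for depends on which happen to stay imbalanced after matching. If everything balances, the reported adjusted odds ratio is in effect unadjusted and close to marginal. If not, it is conditional on whichever variables remained. The odds ratio is non-collapsible, so these are different parameters even without confounding. The set can also change between imputed datasets, and averaging such estimates has no clear meaning. Strong prognostic factors leave the model when balanced, which costs precision in the linear models (NIHSS change) and power in the logistic ones.

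**The sensitivity analysis estimates something else.** Caliper matching without replacement describes patients who can be matched; IPTW in its usual form describes the whole cohort. One odds ratio is conditional and the other marginal. A gap need not mean fragility, and agreement may be chance. At stake is how the main robustness statement of a non-randomised comparison is read.

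**Working it through.** **Step 1. Reproduce the plan's figure.** Rates 0.191 and 0.326, two-sided 0.05, 90% power, pooled variance, mean rate 0.2585:

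n = [1.960·√(2·0.2585·0.7415) + 1.282·√(0.191·0.809 + 0.326·0.674)]² / 0.135² = 218.9, so 219 per group. Then 219 × 1.2 = 263 and 263 × 2 = 526, as stated. The odds ratio implied by these rates is (0.326/0.674)/(0.191/0.809) = 2.05. This is a crude, marginal value.

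**Step 2. Conditional against marginal odds ratio.** Assume a normal prognostic score Z with SD s on the logit scale. Solve E[expit(a + sZ)] = 0.191 for a, then E[expit(a + b + sZ)] = 0.326 for b, with Z standard normal. The marginal odds ratio stays at 2.05. The conditional odds ratio exp(b) is 2.22, 2.43 or 2.72 for s = 0.8, 1.2 or 1.6. The values of s are assumptions.

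**Step 3. Both analyses in simulated cohorts.** Inputs: 842 patients (1,052 less 20%), three measured confounders, a conditional odds ratio of about 2.34, matching as specified, ordinary whole-cohort IPTW, and 600 replicates per scenario. Confounder strengths and effect modification are assumed. About 275 of 420 treated patients found a match.

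| Scenario | Matched, unadjusted | Matched, adjusted | IPTW | Adjusted ÷ unadjusted | Adjusted ÷ IPTW |
|---|---|---|---|---|---|
| Constant effect | 2.10 | 2.33 | 1.96 | 1.11 | 1.19 |
| Effect modification | 2.22 | 2.54 | 2.09 | 1.15 | 1.22 |
| Opposite modification | 2.05 | 2.21 | 1.89 | 1.08 | 1.17 |

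The fourth ratio column shows how far the primary odds ratio moves with the decision to adjust. The last shows the gap that would be read as lack of robustness.

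**Step 4. Population only.** Assume 60% of patients have P(EVT) = 0.7 and an 18-point effect, and 40% have P(EVT) = 0.2 and a 5-point effect.

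- Whole cohort: 0.6·18 + 0.4·5 = 12.8 points.
- Matched sample: stratum 1 has 42% treated and 18% control, so at most 18% form pairs. Stratum 2 has 8% treated and 32% control, so 8% form pairs. The logits (0.85 and −1.39) lie much further apart than the caliper (about 0.22), so no pairs cross strata. Effect: (0.18·18 + 0.08·5)/0.26 = 14.0.
- Matching weights, min(e, 1−e): stratum totals 0.6·0.3 = 0.18 and 0.4·0.2 = 0.08, again 14.0.
- Overlap weights, e(1−e): totals 0.6·0.21 = 0.126 and 0.4·0.16 = 0.064, giving (0.126·18 + 0.064·5)/0.19 = 13.6.

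The gap to ordinary IPTW is 14.0 − 12.8 = 1.2 points. Matching weights remove it, and overlap weights leave 0.4.

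**Step 5. Power lost when a balanced prognostic factor is omitted.** Simulation with 275 assumed pairs, control rate 0.191, 3,000 replicates per setting, and partners sharing none of the prognostic score. With a conditional odds ratio of 2.05, power rises on adjustment from 90% to 94%, 83% to 89% and 73% to 86% for s = 0.8, 1.2 and 1.6, a gain of about 4 to 12 points. If 2.05 is taken as the marginal value, as in Step 1, the gain is only about 2 to 3 points because power is already near 95%. If partners share the prognostic score fully and a pair-robust error is used, the gain is close to nil.

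**The case against.** Matching as primary with IPTW as a sensitivity analysis is common and usefully varies the adjustment method; nothing in Section 2.4 says the two odds ratios must coincide. This stands: the comparison is weak, not worthless. A fuller analysis plan may also name a fixed covariate list or an imbalance threshold. A fixed list would settle the first point. A threshold alone would not, because the selected set would still depend on the data.

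The two halves of the concern also pull against each other. If covariates drop out because they balance, the matched odds ratio is near marginal and the gap to IPTW shrinks. The true marginal odds ratios in Step 3, matched-overlap against whole cohort, are 2.11/1.99, 2.19/2.09 and 2.05/1.90, a gap of 5 to 8%. Fixed adjustment would make the conditional–marginal difference permanent. That is correct, and is why the fix needs a marginal measure as well.

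Three stronger readings are tempting but unsupported:

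- **A reader might infer that pairs are ignored and the intervals are wrong.** The article is silent on variance, which an analysis plan commonly settles. If pairs were ignored, the simulated unadjusted standard error would be 0.194 against an empirical 0.178 to 0.183, about 6 to 9% too large and so conservative. The adjusted one would barely change (0.206 to 0.214, against 0.207 to 0.217 with pair clustering).
- **A reader might equate the matched effect with the effect in the treated.** In Step 4 that would be (0.42·18 + 0.08·5)/0.50 = 15.9, a 3.1-point gap to the whole cohort. It overlooks the caliper and the absence of replacement, under which the matched effect is 14.0.
- **A reader might conclude that weighting to the treated repairs the mismatch.** In Step 4 the gap would grow to 15.9 − 14.0 = 1.9. In the third simulated scenario the treated odds ratio is 1.77, further from the matched 2.05 than the whole-cohort 1.90.

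**Conclusion.** The point holds in this form: the adjustment rule as written leaves the primary conditional odds ratio to be defined by the data, possibly differently across imputations, and the IPTW odds ratio is not the same quantity as the one it checks.

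Under the assumed simulations, the choice to adjust moves the matched odds ratio by 8 to 15%. The adjusted matched and IPTW odds ratios differ by 17 to 22% with no unmeasured confounding. The power lost by omitting balanced prognostic factors ranges from almost none to about 12 points, depending on prognostic strength, the true effect and how closely partners resemble each other. All these sizes rest on assumed confounder and prognostic strengths that the article does not give. That the IPTW targets the whole cohort is the usual default, not something the article states.

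The study is not invalidated. The rule should be changed before outcomes are analysed.

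**What to change.** In Section 2.4, replace adjustment for residual imbalance with a fixed list for every outcome model: age, baseline NIHSS, onset-to-enrollment time, pre-stroke mRS and intravenous thrombolysis. Apply it regardless of balance after matching and identically in all 20 imputed datasets. The first three are already in the propensity model, pre-stroke mRS is checked at screening, and Section 2.2 places thrombolysis before group assignment.

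For the primary outcome, report a standardised (marginal) risk difference beside the odds ratio in both the matched and the weighted analysis. This matches the scale used for sizing and gives a measure that can be compared between the two.

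For the sensitivity analysis, choose weights that target the caliper-matched population, such as matching or overlap weights. If ordinary IPTW is kept, state that its population differs and that a difference in results is not by itself evidence of bias.

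The cost is a few sentences and slightly more analysis work, with no new data or patients.
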